### Interventions

Standard medical therapy will be implemented by attending physicians according to the Chinese official guidelines. This usually involves use of antiplatelet drugs, anti-hypertension drugs, antidiabetic drugs or lipid-lowering drugs etc. Standard medical therapy plus NBP treatment group will add NBP of 200 mg (oral), three times per day for 24 weeks on the basis of conventional treatment. The dose of NBP treatment is consistent with the officially recommended treatment plan for acute ischemic stroke as well as all other NBP clinical trials targeting cognitive impairment [21]. Appropriate number of NBP will be prescribed to ensure they are just enough for the time until next visit and compliance will be assessed by counting empty bottles of NBP at every visit. Blood biochemical tests will be performed at every visit for regular examination and adverse effect monitoring. Previous studies reported a few cases of mild elevation of transaminase after NBP treatment. If this happens, medication will be withdrawn immediately and the condition will be monitored (and treated if necessary) until it returns to normal. This will be treated as drop-out. The schedule of End-PSCI is showed in Fig. 2**.**

**Fig. 2 Fig2:**
[figure not shown]
Schedule of End-PSCI. This is the schedule of End-PSCI trial. After enrolment and allocation, general information will be recorded at baseline. The treatment of standard medical therapy and standard medical therapy combined NBP treatment will last for 24 weeks after stroke. For every follow-up visit (baseline, 6 weeks, 12 weeks and 24 weeks after stroke), vital signs and medical history, application of study drugs, application of combined drugs, NHISS and MRS scores, a set of validated cognitive tests, blood samples collection and adverse events record will be implemented. Carotid Doppler ultrasonography and brain MRI including T1, T2 and T2 Fluid-attenuated inversion recovery imaging will also be performed at baseline and 24 weeks after stroke. NHISS: National Institutes of Health Stroke Scale; MRS: Modified Rankin Scale; MRI: Magnetic Resonance Imaging; FLAIR: axial fluid-attenuated inversion recovery

Notably, long-term use of two types of drugs should be avoided in all enrolled patients. One is that may influence cerebral microcirculation or metabolism such as Nimodipine, Idebenone, Oxiracetam and some traditional Chinese medicine that have blood activating and stasis removing effects. Another type is that may influence cognitive function such as cholinesterase inhibitors, Memantine and antipsychotic drugs. If happens, this will be treated as drop-out.

### Primary outcome

The primary outcome is the difference of incidence of delayed-onset PSCI between two groups after 24 weeks. We here define delayed-onset PSCI as cognitive impairment including mild cognitive impairment and dementia developed in 3–6 months after stroke, without early-onset PSCI. A group of trained neurologists who are blinded from allocation will make the final diagnosis at 24 weeks in the main center based on the Vascular Behavioral and Cognitive Disorders (VASCOG) criterion [25]. Mild cognitive impairment will be diagnosed based on 1) Concerns of a patient, knowledgeable informant, or a clinician of mild levels of decline in ≥1 cognitive domains from a previous level of cognitive functioning, and 2) Evidence of modest deficits in ≥1 cognitive domains on the neuropsychological testing (fall between 1 and 2 standard deviation below the mean (or between the third to 16th percentiles for test scores not normally distributed) of people of similar age, sex, education, and sociocultural background). And The cognitive deficits are not sufficient to interfere with independence (instrumental activities of daily living are preserved). Dementia will be diagnosed based on 1) Concerns of a patient, knowledgeable informant, or a clinician of significant levels of decline in ≥1 cognitive domains from a previous level of cognitive functioning, and 2) Clear and significant deficits in ≥1 cognitive domains on the neuropsychological testing (fall ≥2 standard deviation below the mean (or below the third percentile) of people of similar age, sex, education, and sociocultural background). And the cognitive deficits are sufficient to interfere with independence (e.g. at a minimum requiring assistance with instrumental activities of daily living).

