## Methods

### Design

Effects of NBP on Delayed-onset Post Stroke Cognitive Impairment (End-PSCI) is a prospective, parallel-group, open-label, multicenter, randomized controlled trial with blinded outcome assessment. Hospital patients within 2 weeks of cerebral infarction onset will be randomized into either standard medical therapy group or standard medical therapy combined NBP treatment group. A set of validated cognitive tests and blood samples collection will be implemented at acute phase (within 2 weeks of onset), 6 weeks, 12 weeks and 24 weeks after stroke. Brain magnetic resonance imaging (MRI) including T1, T2 and T2 Fluid-attenuated inversion recovery imaging (most are clinical routine scans with some high resolution, isotropic scans) will also be performed at acute phase and 24 weeks after stroke. An independent Data and Safety Monitoring Board (DSMB) will regularly monitor safety during the study. The trial has been approved by the Institutional Review Board/Ethics Committee in the First Affiliated Hospital of Xi’an Jiaotong University (approval number: XJTU1AF 2020LSK-032). Figure 1 this study is ongoing (recruitment not completed) at the time of submission.

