### Secondary outcomes

The difference of white matter degeneration between two groups after 24 weeks. The degeneration will be reflected by changes of visual scale scores (modified Scheltens Visual Scale) [26] and white matter hyperintensity (WMH) volume from baseline to 24 weeks.The difference of cognitive score changes from baseline to 24 weeks between two groups. Cognitive testing includes Montreal Cognitive Assessment, Beijing Version (MoCA-BJ) [27], Alzheimer’s Disease Assessment Scale-Cognitive Subscale, Chinese version (ADAS-Cog-C) [28], Hamilton depression Rating scale (HAMD-17) [29] and Activities of Daily Living Scale (ADL), Chinese version [30].The difference of prevalence of early-onset PSCI between two groups after 24 weeks. Early-onset PSCI is defined as cognitive impairment including mild cognitive impairment and dementia developed within 3 months after stroke and persistently existed at least for 3 months.

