### Statistical analyses

A customized online database will be used to manage data and SPSS version 25.0 will be used for all analyses. Group t-test, Mann-Whitney u test or χ2 test will be conducted for comparisons between two groups according to different types of variables. Occurrence of delayed-onset and early-onset PSCI will be analyzed as categorical data (yes or no). χ2 test will be used to compare the incidence between two groups and multivariate logistic regression will be used to adjust confounders. Paired sample t-tests or Wilcoxon matched-pairs signed-ranks test will be used to compare WMH degree (visual scale scores and WMH volume) and total cognitive scores at different time point within each group. Changes of WMH degree (indicating degeneration) and total cognitive scores from baseline to 24 weeks will be compared between two groups using Group t-test or Mann-Whitney u test and multivariate linear regression will be used to explore the contributing factors. Changes of cognitive scores will further be dichotomized as improved and unimproved group to do the analysis, improvement is defined as score change < 0 for Alzheimer’s Disease Assessment Scale-Cognitive subscale or > 0 for Montreal cognitive assessment scale. Furthermore, Kaplan–Meier analysis and cox proportional hazards analysis will also be performed to compare the incident rate of any cognitive impairment between two groups and explore contributing factors. Two-sided value of *p* < 0.05 will be considered significant.

Outcomes will be measured both for intention-to-treat population (main analysis population) and the per protocol population. The intention-to-treat population consist of those who have a complete baseline assessment as well as at least one follow-up assessment for the primary outcome variables. Missing values of cognitive scores will be replaced by last observation carried forward method. The per protocol population consist of those who complete the 24-week follow-up with no major protocol violations.

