## Discussion

End-PSCI is designed to assess the preventive effects of NBP on delayed-onset PSCI. To our knowledge, this is the first large randomized controlled trial (RCT) for NBP in PSCI. Previously, a small RCT showed combined NBP treatment could significantly improve the cognitive function 1 month after stroke along with lower serum inflammatory factors [31]. While in this study, cognition was tested at a very short time after stroke which was believed not accurate to reflect the true cognitive function after stroke because of the transient delirium. In 2016, Jia, et al. [21] found NBP significantly increased cognitive scores compared with placebo in patients with subcortical vascular cognitive impairment without dementia in China, after treatment with NBP 200 mg three times daily for 24 weeks. Subcortical vascular cognitive impairment closely associates with CSVD in which white matter injuries play an important role. However, Jia’s trial couldn’t explore the role of white matter injuries in its mechanism due to lack of imaging examination and white-matter-related fluid biomarker tests. In End-PSCI trial, we preserve blood samples at every visit and MRI data at baseline and end time, so that both direct and indirect indications of white matter injuries can be assessed before and after intervention. By doing this, we will provide evidences for NBP’s action on white matter and testify secondary degeneration theory in delayed-onset PSCI.

Treatment duration of NBP is not officially restricted. It varied from 4 weeks to 2 years in different studies targeting cognitive impairment and all showed favorable results [21, 31, 32]. Since this is a preventive study and we have defined delayed-onset PSCI as cognitive impairment occurred in 3–6 months post stroke, we then decide 6 months (24 weeks) of treatment might be appropriate.

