Notably, two types of treatment should be avoided in our study as the first type may act on some same targets with NBP and the second type may influence the cognitive outcomes. The avoidance of first type of treatments will not interfere with the optimal treatments because these are not recommended in routine treatment of cerebral infarction according to the Chinese official guidelines. The second type of treatments are only evidentially recommended in patients with confirmed diagnosis of dementia or mental illness. For patients with confirmed or suspicious diagnosis of newly dementia or mental illness, treatment plan will be determined by doctors and negotiated with patients or caregivers according to patients’ condition. If these treatments are applied, patients will be treated as drop-out, or on the contrary, continue in the study. Confirmed early-onset PSCI patients will continue in the study unless they take medications that should be avoided during the study, which will be recorded and treated as drop-out. With proper informed consent, the treatment plan will be negotiated with these patients or caregivers to decide whether they will continue in the study. These patients will be given routine treatments immediately after the last visit if necessary. Notably, the confirmation of early-onset PSCI will be made at least 3 months after the symptom, and the visit plan is at about 1, 3 and 6 months, which will not significantly delay the treatment.

One drawback of End-PSCI trial is the open-label nature. The main aim of the present study is to investigate the preventive effects of NBP on delayed-onset PSCI, and the primary outcome is defined as the difference of incidence of delayed-onset PSCI between study group and control group. However, due to the lower incidence of delayed-onset PSCI, the sample size would be about 3000 patients with acute cerebral infarction from the calculation based on the primary outcome, therefore will cost too much to provide placebo medicines. Hence, we design this study as open label. To avoid bias, efforts have been made by blinded outcome assessment that allocation will be blinded from all cognitive evaluators and senior neurologists who make the final diagnosis.

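### Delayed-onset PSCI counts only in patients free of early-onset PSCI, a post-randomisation outcome NBP may change, so a shift in onset time can mimic or mask prevention

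*Protocol article*

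**What the plan says.** The Primary outcome section restricts the event: "We here define delayed-onset PSCI as cognitive impairment including mild cognitive impairment and dementia developed in 3–6 months after stroke, without early-onset PSCI". The Secondary outcomes section defines early-onset PSCI as impairment "developed within 3 months after stroke and persistently existed at least for 3 months", and lists it as a treatment comparison in its own right: "The difference of prevalence of early-onset PSCI between two groups after 24 weeks".

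Patients are randomised within 2 weeks of stroke and treated to week 24 (Patient population; Interventions), so early-onset status develops on treatment. Cognition is tested "at acute phase (within 2 weeks of onset), 6 weeks, 12 weeks and 24 weeks after stroke" (Design). The Discussion calls these visits about 1, 3 and 6 months, equates 6 months with 24 weeks, and adds that "the confirmation of early-onset PSCI will be made at least 3 months after the symptom". It also cites earlier evidence that "a small RCT showed combined NBP treatment could significantly improve the cognitive function 1 month after stroke", while doubting the accuracy of testing that early.

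On analysis the article says: "Occurrence of delayed-onset and early-onset PSCI will be analyzed as categorical data (yes or no"). A chi-square test compares incidence. The text does not say whether an early-onset case is a non-event for the primary outcome or leaves the denominator. Early-onset patients stay in the study unless they take drugs to be avoided, in which case they become drop-outs (Discussion). Any cognitive impairment is compared only in an additional Kaplan–Meier and Cox analysis.

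**The concern.** The trial is meant to show that NBP prevents delayed-onset PSCI. Whether a patient can have that event depends on what happens in the first 3 months of treatment. A drug that prevents or postpones early impairment leaves more vulnerable patients able to become delayed-onset cases, and so looks weaker than it is. A drug that only moves onset from after 3 months to before 3 months empties the delayed-onset category without sparing anyone. The primary test cannot tell these apart from true prevention, and nothing in the article ties the conclusion to the total number of impaired patients.

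The border between the two categories falls on a visit, with no tolerance, and some courses of impairment fit neither definition.

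**Working it through.** **Inputs.** From the article: control rate 4.4%, 50% reduction to 2.2%, 1200 per group, 20% drop-out, 1:1 allocation, two-sided 5%, visits at weeks 6, 12 and 24. The article gives no power and no early-onset rate. Early-onset rates, prevented fractions, conversion rates and onset shifts below are assumptions.

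**1. The plan's own figure.** n per group = [z(0.975)·√(2p̄(1−p̄)) + z(power)·√(p₁(1−p₁)+p₂(1−p₂))]² / (p₁−p₂)², with p₁ = 0.044, p₂ = 0.022, p̄ = 0.033. This gives 1034 at 80% power, 1183 at 85% and 1384 at 90%. The stated 1200 corresponds to 85.5% power, and 2400/0.80 = 3000 as stated. The baseline for what follows is 86%.

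**2. Timing.** Week 12 is day 84 and week 24 is day 168, so impairment first seen at week 12 can be followed for 168 − 84 = 84 days. With 24 weeks = 6 months, 3 months is 12 weeks = 84 days, and the persistence rule is met exactly. A week-24 visit a few days early fails it. With calendar months (about 91 days) it would never be met. Impairment present at week 6, absent at week 12 and present at week 24 is not persistent, so not clearly early-onset. It also did not first develop after 3 months, so it is not clearly delayed-onset.

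**3. Distortion against NBP.** All patients stay in the denominator. Assume 30% early-onset in controls, of which NBP prevents a fifth: 0.30 × 0.20 = 6% of patients are spared. Let a fraction c of them become impaired after 3 months. NBP's delayed-onset rate is then 0.022 + 0.06c.

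| c (assumed) | NBP delayed-onset | Power vs 4.4% | Any PSCI, control vs NBP |
|---|---|---|---|
| 0 (no early effect) | 2.2% | 86% | 34.4% vs 32.2% |
| 3% | 2.4% | 78% | 34.4% vs 26.4% |
| 10% | 2.8% | 56% | 34.4% vs 26.8% |
| 20% | 3.4% | 24% | 34.4% vs 27.4% |

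Any PSCI is 0.30 + 0.044 in controls. On NBP it is 0.24 plus the delayed-onset rate (0.30 + 0.022 in the first row). For scale, the risk among patients free of early-onset PSCI would be 2.2/70 = 3.1% on NBP and 4.4/70 = 6.3% in controls. At c = 20%, moving the early-onset rate from 20% to 40% moves power from 44% to 11%.

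**4. Distortion in favour of NBP.** NBP prevents nobody, but a fraction q of its delayed cases surface before 3 months. The observed rate is 0.044 × (1 − q): 4.0%, 3.3% and 2.2% for q = 10%, 25% and 50%. For q = 50%: z = (0.044 − 0.022)/√(2 × 0.033 × 0.967/1200) = 0.022/0.00729 = 3.02, p = 0.003. For q = 10% and 25%, p = 0.59 and 0.16. Any PSCI is equal in both arms throughout; with 30% early-onset it is 30 + 4.4 = 34.4% in controls and 32.2 + 2.2 = 34.4% on NBP.

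**5. Early-onset cases removed instead.** At 30% early-onset, 1200 × 0.70 = 840 per arm remain. If 4.4% and 2.2% apply to those remaining, power is 71%. The larger problem is selection: the patients compared were chosen by a status that treatment may have changed.

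**The case against.** The strongest reply is that targeting delayed-onset PSCI is deliberate, because the Background argues that it may have a different mechanism. If everyone stays in the denominator, the chi-square test is a valid randomised comparison of that outcome. Early-onset PSCI is already a secondary outcome, any impairment is already analysed over time, and a blinded central group makes the diagnosis. This stands as far as it goes. What remains is interpretation: those analyses could reveal a shift in timing, but the prevention claim does not depend on them.

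Several stronger readings are tempting and not supported:

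- A reader might infer that impairment first seen at week 12 can never be early-onset, or becomes delayed-onset by default. On the article's own week-to-month convention it just qualifies, and the delayed-onset definition requires development at 3–6 months. The defect is the absence of margin.
- A reader might infer that early-onset cases are counted as non-events. The article says only that occurrence is yes or no.
- A reader might infer that unblinded investigators can choose a patient's category through the visit date. They are responsible for follow-up visits, but the visits are scheduled and nothing says that the dates are discretionary.
- A reader might take the fall to 24% power as the expected loss. It needs 20% conversion among spared patients, about six times the 3.1% in step 3; at 3–10% conversion power is 78–56%.
- A reader might infer that NBP brings impairment forward. Nothing in the article suggests it. Step 4 shows only that the primary test could not detect it.

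**Conclusion.** The point holds as a matter of definition and interpretation, and should be fixed. The primary event depends on a post-randomisation status that NBP may change, the handling of that status in the denominator is unstated, and the two definitions do not sort every patient on the visit schedule. That distortion can run in either direction follows from the definitions. Its size does not: the 78–24% power range and the 4.4% against 2.2% result rest on assumed early-onset rates, prevented fractions, conversion rates and onset shifts. The documents do not show that the comparison will mislead, only that as defined it could, and that the primary result alone would not reveal it.

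**What to change.** Have the blinded diagnostic group classify every patient by scheduled visit (weeks 6, 12, 24) into exclusive categories:

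- **Early-onset:** impaired at week 12, whether or not at week 6, and still impaired at week 24.
- **Delayed-onset:** unimpaired at weeks 6 and 12, impaired at week 24.
- **Transient:** impaired at week 6 or 12, not at week 24.
- **Recurrent:** impaired at week 6, unimpaired at week 12, impaired at week 24; reported separately and not counted as delayed-onset.

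With unimpaired at all three visits as the remaining class, these cover all eight patterns. They also replace the month-based border, so a week-24 visit a few days early no longer changes the category. Requiring impairment at both weeks 12 and 24 keeps the article's persistence condition for early-onset PSCI.

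State that all randomised patients form the denominator of the primary test. Add any PSCI at week 24 (early, delayed or recurrent) as the first key secondary outcome and report it beside the primary. Claim that NBP prevents PSCI, rather than changes its timing, only if any PSCI is also lower on NBP.

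The cognitive tests are already scheduled at each visit, and recruitment was not complete at submission. The cost is revised wording, classification at each visit by the existing group, one extra table, and a prevention claim that is slightly harder to make.

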### Secondary outcomes

The difference of white matter degeneration between two groups after 24 weeks. The degeneration will be reflected by changes of visual scale scores (modified Scheltens Visual Scale) [26] and white matter hyperintensity (WMH) volume from baseline to 24 weeks.The difference of cognitive score changes from baseline to 24 weeks between two groups. Cognitive testing includes Montreal Cognitive Assessment, Beijing Version (MoCA-BJ) [27], Alzheimer’s Disease Assessment Scale-Cognitive Subscale, Chinese version (ADAS-Cog-C) [28], Hamilton depression Rating scale (HAMD-17) [29] and Activities of Daily Living Scale (ADL), Chinese version [30].The difference of prevalence of early-onset PSCI between two groups after 24 weeks. Early-onset PSCI is defined as cognitive impairment including mild cognitive impairment and dementia developed within 3 months after stroke and persistently existed at least for 3 months.

### Data monitoring body

A Steering Committee chaired by [name] from the First Affiliated Hospital of Xi’an Jiaotong University will take charge of overall design, co-ordination, financial management and publications.

The independent DSMB, consisting of experienced neurologists, academic members and an independent statistician, will meet every 6 months to assess progression, data quality, safety and efficacy of the trial. Recommendations on whether to continue or stop the trial will be given to the steering committee. All adverse events will be recorded and managed properly until they are resolved or reach stability.

### Sample size

Previous studies showed that the prevalence of delayed-onset PSD ranged from 4.4 to 23.9% [6]. We chose 4.4, 10.0 and 23.9% with the hypothesized effect size of 20, 30, and 50% reduction for NBP to do the calculation [21]. Considering the feasibility, 4.4% of the incident rate and reduction of 50% were used in the end, then 1200 cases for per group could meet the statistical requirement. A drop-out rate of 20% was also considered, then 3000 cases in total were required.

